## Abstract

**Background:**

After esophagectomy for esophageal and esophagogastric cancer, more than half of patients have lost > 10% of their body weight at 12 months. In most cases, the gastric remnant is used for reconstruction after esophagectomy. One of the most serious nutritional complications of this technique is delayed gastric emptying caused by gastric remnant mobilization and denervation of the vagus nerve. The aim of the PYloroplasty versus No Intervention in GAstric REmnant REconstruction after Oesophagectomy (PYNI-GAREREO) trial is to analyze the clinical outcome of modified Horsley pyloroplasty (mH-P) as a method of preventing delayed gastric emptying.

**Methods:**

The PYNI-GAREREO trial is designed as an open randomized, single-center superiority trial. Patients will be randomly allocated to undergo gastric remnant reconstruction with mH-P (intervention group) or no intervention (control group) in parallel groups. All patients with esophageal cancer or esophagogastric cancer planning to undergo curative minimally invasive esophagectomy will be considered for inclusion. A total of 140 patients will be included in the study and randomized between the groups in a 1:1 ratio. The primary outcome is the body weight change at 6 months postoperatively, and the secondary outcomes are the nutritional status, postoperative complications, functional outcome, and quality of life until 1 year postoperatively.

**Discussion:**

We hypothesize that mH-P after minimally invasive esophagectomy more effectively maintains patients’ nutritional status than no pyloroplasty.

**Trial registration:**

UMIN Clinical Trials Registry UMIN000045104. Registered on 25 August 2021. https://center6.umin.ac.jp/cgi-open-bin/ctr_e/ctr_view.cgi?recptno=R000051346.

**Supplementary Information:**

The online version contains supplementary material available at 10.1186/s13063-023-07435-5.

## Background

### Background and rationale

Esophagectomy and reconstruction are necessary for the radical treatment of esophageal cancer or esophagogastric junction cancer. Improved outcomes after minimally invasive esophagectomy (MIE) have been observed during the last two decades, and nutritional considerations in these patients have thus become important. Most patients have lost 5 to 12% of their body weight at 6 months postoperatively, and more than half of patients have lost > 10% of their body weight at 12 months [1]. In most cases, the gastric remnant is used for reconstruction; however, delayed gastric emptying (DGE) may be caused by gastric remnant mobilization and denervation of the vagus nerve [2–4].

DGE can induce anastomotic leakage by negative impact pressure from gastric contents. In the long term, low oral intake might worsen patients’ nutritional status and result in decreasing cancer immunity. However, there is no evidence of efficient ways to prevent DGE [5–8]. Therefore, for the prevention of DGE after MIE and gastric remnant reconstruction, we plan to preliminarily perform modified Horsley pyloroplasty (mH-P) [9].

### Objectives

The aim of the PYloroplasty versus No Intervention in GAstric REmnant REconstruction after Oesophagectomy (PYNI-GAREREO) trial is to compare the postoperative change in body weight between patients undergoing mH-P and no intervention (NI). The change in body weight after mH-P mainly reflects the nutritional status caused by the change in oral intake. The primary outcome is the rate of body weight loss at 6 months postoperatively.

## Methods/design

### Trial design

The PYNI-GAREREO trial is designed as an open randomized, single-center superiority phase III trial. Patients will be randomly allocated to undergo gastric remnant reconstruction with mH-P or NI in parallel groups.

## Methods: participants, interventions, and outcomes

### Study setting

The PYNI-GAREREO trial will be conducted in Teine Keijinkai Hospital as a single-center, two-arm, open-label, randomized phase III superiority trial. Table 1 (SPIRIT) shows the schedule of enrollment, interventions, and assessments. The SPIRIT reporting guidelines were used for this study protocol [10]. The SPIRIT checklist is provided as Additional file 1.

**Table 1 Tab1:** The schedule of enrollment, interventions, and assessments

Time point	Enrollment and allocation	Study period						
		**Post-allocation**						**Close-out**
	*** − 28 days***	**Surgery**	***2 weeks*** ** ± ** ***5 days***	***1 month***	***3 month***	***6 month***	***9 month***	***12 month***
**Enrollment**								
**Eligibility screen**	X							
**Informed consent**	X							
**Allocation**	X							
**Interventions**								
***mH-pyroloplasty***		X						
***No intervention***		X						
**Assessments**								
**Baseline patient characteristics**	X							
**Baseline tumor characteristics**	X							
**Body composition**	X		X	X	X	X	X	X
**Laboratory data**	X		X	X	X	X	X	X
**Postoperative outcome data**		X	X					
**Pathological data**			X					
**Oncological follow-up data**				X	X	X	X	X
**Gastroendoscopy**						X		X
**Computed tomography**				X	X	X	X	X
**QOL questionnaires**			X	X	X	X	X	X

### Eligibility criteria

#### Population

All male or female patients with resectable esophageal carcinoma or esophagogastric junction cancer will be screened for eligibility by two esophageal surgeons. The patients will undergo MIE and gastric remnant reconstruction for radical treatment of esophageal cancer or esophagogastric cancer. Two expert esophageal surgeons ([name]) will perform or assist all interventions.

#### TNM clinical classification

The clinical TNM classification will be evaluated by radiological imaging and endoscopy based on the eighth edition of the TNM classification.

The following are the inclusion criteria:Reconstruction by the posterior sternal routeNo previous laparotomy with a high degree of adhesion (e.g., traumatic incision for trauma surgery, duodenal ulcer perforation, or gastrectomy)Age of ≥ 18 years at the time of providing informed consentEastern Cooperative Oncology Group performance status of 0 or 1Treatment by thoracoscopic or robot-assisted thoracic MIEAbdominal operation by manual laparoscopy or laparoscopyAnastomosis by the cervical anastomosis techniqueFull understanding of the study and voluntary provision of written consent to participate in the study

The following are the exclusion criteria:Swallowing problems and poor oral intake associated with swallowing dysfunctionWeight loss of ≥ 20% within 6 months before surgeryAny synchronous active advanced cancer or diseases that affect the nutritional statusMedical history of DGESimultaneous resection for gastric cancer, other pyloroplasty procedures (e.g., finger bougie technique, Heineke–Mikulicz strictureplasty, or botulinum toxin injection), or Roux-en-Y reconstruction during the trialClinical condition inappropriate for participation in this study as judged by the patient’s physician

#### Informed consent

Operators and clinical research coordinators (CRCs) will obtain informed consent or assent from potential trial participants. The operators will explain the procedure, and the CRCs will supportively explain the concept of the trial. The operators and CRCs will inform the potential participants of the trial after the operation schedule has been determined; the information will be provided about 2 weeks before the operation date. The operators and CRCs will give the trial document, patient information sheet, and illustrated schema to the participants. At 1 or 2 days after obtaining informed consent from the participants, the CRCs will re-confirm the participants’ understanding and obtain the document of approval.

#### Randomization

After confirmation of the eligibility criteria, registration will be completed by a web-based system to the UMIN Clinical Trials Registry system. The CRCs will enter the registration details into the system. The minimization method will be used for randomization. The staff member who will assess the blinded medical reports will also be blinded. Patients will be randomized to the intervention group or control group in a 1:1 ratio using a computerized randomization tool (UMIN INDICE cloud) with the minimization method, balancing the arms according to age, clinical TNM stage, and change in preoperative body weight during the most recent 6 months before surgery. The two arms will be the mH-P arm (intervention) and the NI arm (control). Because this trial will involve different surgical techniques, complete blinding of the treating surgeons and medical staff is not feasible. The surgeon will know which operation has been performed, and the medical staff can determine whether the patients have undergone pyloroplasty or not by reading the official medical records. However, a study team member will assess blinded medical reports regarding mH-P or NI to ensure a blinded assessment of the primary outcome parameter.

#### Pyloroplasty procedure

For gastric remnant reconstruction, mH-P either will or will not be performed according to the randomization result. mH-P will be performed by first longitudinally cutting all gastric wall layers to a length of 3 cm at 1.5 cm above and below the pyloric ring; the surgical wound will then be closed using seven to nine absorbable monofilament sutures (4–0 PDS®) in a horizontal Gambee pattern. Intraoperative botulinum injection and application of a pyloric ring finger bougie will be prohibited during the trial.

#### Decompression tube placement and jejunostomy

We will routinely perform decompression tube placement and jejunostomy of the gastric remnant. After mobilization of the stomach, we will cut the gastric serosa and muscular layer. We will then cut the point of the mucosa layer and insert two tubes: the decompression tube (inserted cranially) and the enteral tube (inserted caudally toward the jejunum). The two tubes will be placed in the gastric remnant wall by the Witzel procedure. Finally, after the reconstruction and cervical anastomosis, we will perform abdominal wall plasty of the gastric remnant with the placement of tubes.

#### Criteria for discontinuing or modifying allocated interventions

If non-inferiority of the mH-P group to the NI group for the primary endpoint is demonstrated, and even if superiority is demonstrated in the interim, the study will be stopped (active discontinuation). In such a case, the need for discontinuation of the trial will be comprehensively considered without being restricted by the statistical judgment of the trial or other factors. If the trial is discontinued, the results will be reported. The enrolled patients will be followed up for 1 year.

#### Provisions for post-trial care

In the event that a research participant suffers health damage as a result of the conduct of the research, the physician in charge of the research will provide appropriate treatment and investigate the cause of the damage. In such cases, if treatment or examination becomes necessary, it will be conducted within the scope of the research participant’s normal insurance treatment. Examples of health damage include dumping syndrome or bile reflux after pyloroplasty as well as leakage at the pyloroplasty point.

### Outcomes

The primary endpoint is the rate of body weight loss at 6 months after surgery. The secondary endpoints are oral intake and change in nutritional status, which will be checked during the perioperative hospitalization period and at 1, 3, 6, 9, and 12 months after surgery.

Oral intake will be calculated as a percentage of total energy expenditure, which will be calculated based on the weight and activity coefficient of each patient, and data will be collected at each time point. As the nutritional status of the patient will be monitored by body composition which is analyzed by a bioimpedance analyzer (InBody S10®). The analyzer determines the total body fat mass (kg) and skeletal muscle index (kg/m^2^). Additionally, blood tests will be performed at fixed points to measure nutritional evaluation indices (albumin, pre-albumin, cholesterol, total protein, lymphocyte count, and C-reactive protein).

Intraoperative factors such as the total blood loss, operation time, thoracic approach, subtotal gastric remnant or gastric tube reconstruction, and inclusion or exclusion of Kocher mobilization will also be analyzed.

To evaluate the degree of pyloric transit as a secondary endpoint, the amount and nature of decompressed gastric drainage and the pH and bilirubin level of the drainage will be measured on postoperative days 1, 3, 5, and 7. On day 7, the degree of pyloric drainage and the presence or absence of reflux will be assessed by oral contrast according to the standard clinical path. The blood and gastric drainage measurements will be taken in the laboratory, the data will be recorded in the medical record, and the sample will be discarded. The decompression tube will be clamped at 6:00 am to equalize the condition of the reconstructed elevated stomach, and contrast examination will be performed at 9:00 am on the same day. The contrast medium will be barium diluted to 60%.

The pyloric transit (an objective index) as evaluated by oral barium contrast will be scored according to the presence or absence of gastric contents in the reconstructed elevated stomach at the beginning of the examination (0: no, 1: yes), the pyloric transit time of the contrast medium (0: < 1 s, 1: > 1 s), and stagnation of the contrast medium in the stomach (0: completely disappears; 1: more than half remains; 2: all remains).

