### Follow-up

For each participant, the study will start at randomization, and the patient will be followed until 12 months after surgery. The primary outcome parameter will be evaluated every 3 months after surgery. During the 1 year of follow-up, data on readmission, functional results, and quality of life will be generated. Study visits will be scheduled to take place 4 weeks before surgery and 1, 3, 6, 9, and 12 months after surgery. The functional outcomes are the pyloric transit, bile reflux, oral intake, and gastrointestinal symptom questionnaires.

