### Statistical methods

The Mann–Whitney *U*-test will be used to compare continuous variables such as weight change, which is the primary endpoint; body composition; and blood test indices. Student’s *t*-test (two-tailed) will be used to compare the mean parameters, and the chi-square test will be used to compare the bivariate variables such as the presence of perioperative complications.

Further subgroup analysis will only be carried out in case of significant interaction effects. The Wilcoxon signed rank test will be used to determine significant effects. Comparisons between the mH-P and control group for weight change either pre- or postoperative 6 months will be performed. Differences with a *p* < 0.050 are considered statistically significant.

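### Day-7 pyloric transit time is coded only as below or above 1 s, so short and long delays beyond 1 s look the same on this item of a secondary endpoint

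*Protocol article*

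**What the plan says.** The Outcomes section introduces the relevant measurements with "To evaluate the degree of pyloric transit as a secondary endpoint", and the Follow-up section repeats the status: "The functional outcomes are the pyloric transit, bile reflux, oral intake, and gastrointestinal symptom questionnaires". The day-7 contrast examination is standardised, with the decompression tube clamped at 6:00, the examination at 9:00 and barium diluted to 60%. Three items are scored:

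- gastric contents at the start, coded 0/1;
- "the pyloric transit time of the contrast medium (0: < 1 s, 1: > 1 s";
- "stagnation of the contrast medium in the stomach (0: completely disappears; 1: more than half remains; 2: all remains".

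The same endpoint also draws on the drainage fluid, sampled on days 1, 3, 5 and 7 after surgery: "the amount and nature of decompressed gastric drainage and the pH and bilirubin level of the drainage will be measured". Later, residue is assessed by CT at 1, 3, 6, 9 and 12 months, and residue and transit by endoscopy at 6 and 12 months.

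Under Statistical methods, the Mann–Whitney test "will be used to compare continuous variables such as weight change, which is the primary endpoint; body composition; and blood test indices", and "the chi-square test will be used to compare the bivariate variables such as the presence of perioperative complications". The article does not say whether the three items are summed, whether any item is tested alone, or whether the seconds are kept.

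**The concern.** Time to cross the pylorus is a graded quantity, measured where the pyloroplasty acts. The trial is about delayed emptying, and the delayed patients lie on the side of the cut that is collapsed into a single code. No rationale or validation for 1 s is given. If most patients in both arms exceed 1 s, the item will hardly separate them, even if pyloroplasty shortens the delay.

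What is at stake is the sensitivity of one component of a secondary endpoint. It still matters because the Discussion says the trial will investigate whether pyloric passage improves. It also cannot be left to a later analysis plan, which can analyse seconds only if someone wrote them down.

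**Working it through.** **No figure to reproduce.** The article states no power, expected share above 1 s or effect size for pyloric transit. The 60 and 70 per arm under Sample size are for 6-month weight. What follows is therefore an illustration under stated assumptions.

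**Inputs from the article.** 70 per arm, 1:1 allocation, two-sided 0.05, Mann–Whitney for continuous variables, chi-square for two-category variables.

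**Assumptions.** On some monotone scale, such as the log, transit time is normal with equal SD, and pyloroplasty shifts it by d SD. The share of controls above 1 s, p1, runs from 50% to 95%. The 0/1 item is tested alone by chi-square, which the article does not state.

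**Formulas.**

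- Shift giving 80% power on the full scale: d = (1.960 + 0.842) × √(2/70) = 0.474.
- Mann–Whitney power ≈ Φ(d × √(3n/2π) − 1.960) = Φ(0.474 × 5.78 − 1.960) = 78%.
- Share above 1 s with pyloroplasty: p2 = Φ(Φ⁻¹(p1) − d).
- Chi-square power ≈ Φ{[(p1 − p2) − 1.960 × √(2p̄(1−p̄)/n)] / √([p1(1−p1) + p2(1−p2)]/n)}, where p̄ is the mean of p1 and p2.

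Example: p1 = 0.50 gives p2 = 0.318 and p̄ = 0.409, so power ≈ Φ[(0.182 − 1.960 × 0.0831)/0.0817] ≈ 59%.

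**Results, d = 0.474 (Mann–Whitney 78%).**

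| Controls above 1 s | p2 | Chi-square power | Loss, points |
|---|---|---|---|
| 50% | 0.318 | 59% | 19 |
| 70% | 0.520 | 59% | 19 |
| 80% | 0.644 | 54% | 24 |
| 90% | 0.790 | 43% | 35 |
| 95% | 0.879 | 32% | 46 |

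**Results, d = 1.0 (Mann–Whitney about 100%).**

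| Controls above 1 s | p2 | Chi-square power | Loss, points |
|---|---|---|---|
| 50% | 0.159 | 99% | 1 |
| 70% | 0.317 | 99.7% | under 1 |
| 90% | 0.611 | 98% | 2 |
| 95% | 0.740 | 94% | 6 |

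**Check by simulation.** These formulas are approximate when the proportions are extreme, so I simulated 20,000 trials per setting with the uncorrected chi-square test. The loss ran from 18 to 44 points at d = 0.474 and from 18 to 46 at d = 0.5. At d = 1.0 it was at most about 4 points. I therefore quote about 17 to 45 points for a shift near 0.5 SD and at most about 4 for a shift of 1 SD.

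**Why the position of the cut matters.** The large-sample efficiency of the cut relative to the full scale is φ(t)²/[p(1−p)], with t the normal quantile at the cut. It is 0.64 at the median, 0.49 at 80%, 0.34 at 90% and 0.22 at 95%.

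**Combined score.** The loss would be smaller because the other items contribute. I give no figure, since the article says neither how the items are combined nor how they relate to each other.

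**The case against.** Three objections carry weight.

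1. **Other measures grade the same thing.** A reader might infer that graded delay cannot be compared at all, or that a weight result would be left without a mechanism. The documents do not support that. The stagnation item has three levels and can separate patients who share the transit-time code. Drainage amount, pH and bilirubin are not dichotomised, and CT and endoscopy add later readings. This stands in full.

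2. **The power figures are not the protocol's.** A reader might infer that the measure loses much of its power. That depends on an effect size and a distribution that the article does not give, and on a stand-alone chi-square test that it does not specify. If the effect on transit is large, which is plausible because the operation acts on the pylorus itself, little is lost unless 1 s lies far in the tail. This also stands, so the range is illustrative.

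3. **Silence is not discarding.** A condensed article need not list every case record form field, and the full protocol may keep the seconds. That is possible. But the article does state the scoring rule for this item, and the rule is binary. If seconds are already recorded, one sentence settles the matter.

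A practical objection is that timing needs a defined start and end, which the article does not give, and that the physician doing the imaging is not blinded. Both apply equally to judging whether a time is above or below 1 s.

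**Conclusion.** The point holds as a low-priority improvement. The stated scoring reduces transit time to 0/1 at an unexplained 1 s cut, and on this item all grading beyond 1 s is lost. The effect is confined to one item of a score for a secondary endpoint with no claimed power. The primary endpoint, its analysis and the sample size are untouched.

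The size rests on assumed normality on a monotone scale, an assumed shift, 50% to 95% of controls above 1 s, and a stand-alone test. With 70 per arm the loss then ranges from negligible (at most about 4 points at 1 SD) to substantial (about 17 to 45 points near 0.5 SD, rising as 1 s moves into the tail). The documents do not show where in this range the trial lies. That uncertainty is itself a reason to keep the seconds.

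**What to change.** In the Outcomes section:

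- State that the pyloric transit time is recorded in seconds during the existing day-7 contrast examination, and define the start and the end of observation.
- Rank no passage by the end of observation as the longest value.
- Compare the arms on this time by the Mann–Whitney test already given under Statistical methods. It needs only ranks, so skewness and non-passage cause no difficulty.
- Keep the 0/1 code as a component of the score, and give the reason for 1 s.

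The cost is one more case record form field, a sentence or two of text and a more careful reading of the time. No extra examination or visit is needed. Recruitment is open, so patients already examined will keep only the 0/1 code unless their seconds were noted or can be read from stored images. The number with a recorded time should be reported by arm.

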Do you break out in a cold sweat within about 30 min after eating?	□	□	□	□	□
Do you experience palpitations within approximately 30 min after eating?	□	□	□	□	□
Do you experience dizziness within approximately 30 min after eating?	□	□	□	□	□
Does your stomach rumble within about 30 min after eating?	□	□	□	□	□
Do you have abdominal pain within about 30 min after eating?	□	□	□	□	□
Does your whole body become sluggish and weak 2 to 3 h after eating?	□	□	□	□	□
Do you feel sleepy 2 to 3 h after eating?	□	□	□	□	□
Do you break out in a cold sweat 2 to 3 h after eating?	□	□	□	□	□
Do you have diarrhea?	□	□	□	□	□

The short-term outcomes evaluated in this study will be postoperative complications and the length of hospital stay. Postoperative complications in this trial are defined as anastomotic leakage, stricture, pneumonia, recurrent nerve palsy, surgical site infection, and chylothorax.

The routinely placed jejunostomy enteral tube will be removed within 3 months postoperatively in the outpatient clinic when the patient has been determined to have no risk of reduced oral intake. If the tube feeding is used for a longer period, the prolonged time will be one of the outcome parameters.

Long-term recurrence and the prognosis will also be followed up.

Patients will be blinded to which group they are in, but the physician who performs the surgery and performs the imaging and follow-up will not be blinded to whether pyloroplasty is performed. The dietitian, nurse, and data analyst who evaluate the nutritional status and gastrointestinal symptoms will be blinded to which group each patient is in.

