### Oversight and monitoring

An independent data and safety monitoring committee will evaluate the progress of the trial and examine safety variables. The committee will consist of a surgeon, CRCs, and a statistician. Individualized patient description charts including safety parameters will be presented to the committee, including one table comprising these endpoints in blinded groups every 6 months. The main safety parameters are all serious adverse events (AE): mortality, multiple organ failure, anastomotic leakage, pulmonary complications, cardiovascular complications, reinterventions, and reoperation. After the investigators have presented the data, the members of the committee will discuss these results in the absence of the investigators and will then advise them. Possible options will include continuing the trial, performing an interim analysis, adjusting the trial’s design, and discontinuing the trial. Discontinuation will be advised if the committee concludes that the results would convince a broad range of clinicians that one trial arm is inferior or if safety is compromised in one arm. If the committee advises adjustment of the trial’s design, performance of an interim analysis, or discontinuation of the trial, the responsible medical ethical committee will also be notified. Serious adverse events (SAE) will be reported to the chairman of the hospital. The PYNI-GAREREO trial will be monitored according to the Japanese ethical guidelines for medical and health research involving human subjects. This is a low-risk study because both interventions being investigated are considered to be standard care in Japan.

In-house monitoring will be performed every year by a third party to evaluate and improve the progress and quality of the study. A Patient and Public Involvement (PPI) member will not be part of the committee.

The first interim analysis will be conducted after half of the planned number of patients are enrolled, and the second interim analysis will be conducted immediately before the planned patient accrual is completed. The data and safety monitoring committee will review the interim analysis reports independently from the investigators and statistician. In-house monitoring will be performed every 6 months by a data center to evaluate and improve the study progress, data integrity, and patient safety.

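### The six-item complication definition does not name leakage at the pyloroplasty site, a harm only the mH-P arm can have, so for that event the complication comparison can err only in favour of mH-P

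*Protocol article*

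**What the plan says.** The protocol article's Outcomes section introduces complications and length of stay as the short-term outcomes and then defines the former: "Postoperative complications in this trial are defined as anastomotic leakage, stricture, pneumonia, recurrent nerve palsy, surgical site infection, and chylothorax". The wording is that of a definition, with nothing to mark the six events as examples. The abstract and the trial registration table (Table 3) both place postoperative complications among the secondary outcomes. Statistical methods assigns a chi-square test to the presence of complications.

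The harms of the procedure are described elsewhere. Provisions for post-trial care states: "Examples of health damage include dumping syndrome or bile reflux after pyloroplasty as well as leakage at the pyloroplasty point". Oversight and monitoring sets out what the committee sees: "The main safety parameters are all serious adverse events (AE): mortality, multiple organ failure, anastomotic leakage, pulmonary complications, cardiovascular complications, reinterventions, and reoperation". The Safety section defines adverse and serious adverse events in general terms and says that both will be collected.

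Two of the three harms named under post-trial care also appear as outcomes. Follow-up states: "The functional outcomes are the pyloric transit, bile reflux, oral intake, and gastrointestinal symptom questionnaires". The Outcomes section adds that "the pH and bilirubin level of the drainage will be measured on postoperative days 1, 3, 5, and 7" and that, on day 7, "the presence or absence of reflux will be assessed by oral contrast according to the standard clinical path". Table 2 asks about symptoms soon after meals (for example "Do you break out in a cold sweat within about 30 min after eating") and later (for example "Does your whole body become sluggish and weak 2 to 3 h after eating").

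**The concern.** A complication outcome that compares an added surgical step with its absence should be able to count what that step can cause. Here the list includes the leak that the trial hopes to prevent: Background and Discussion both argue that delayed emptying may provoke anastomotic leakage, and the Discussion says its incidence will be studied. The list does not name the leak that the added step can create.

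Control patients have no pyloroplasty, so the omission cannot balance between arms. The trial could report similar complication rates, or a lower rate with mH-P, from a total that leaves out the one leak specific to the intervention. This matters because the Discussion foresees that mH-P might become a standard additional procedure. The article states the definition outright, so this is a stated rule that can miscount, not a detail left to a fuller document.

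**Working it through.** No figure in the article is at issue. The main check is a comparison of texts, and the arithmetic after it only gives scale.

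**1. Is the event covered by a listed item?** The nearest is anastomotic leakage. The eligibility criteria and the section on decompression tubes identify the anastomosis as the cervical one. The pyloroplasty is described separately, as a 3 cm cut through the full gastric wall closed with seven to nine sutures, and Provisions for post-trial care gives its leak a name of its own. The listed term therefore does not plainly include it. A leak might be recorded as surgical site infection, but nothing says that it will be.

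**2. Where does each harm named under post-trial care appear?**

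| Harm | In the six-item list | A named outcome elsewhere | Arms in which it can occur |
|---|---|---|---|
| Bile reflux | No | Yes: functional outcome, drainage bilirubin and pH, day-7 contrast study, one Table 2 item | Both |
| Dumping syndrome | No | Yes, as symptoms: five Table 2 items at about 30 minutes, three at 2 to 3 hours, and diarrhea | Both |
| Leakage at the pyloroplasty site | No | No | mH-P only |

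None of the three is in the list. Two of the three are measured in both arms by other means. One is a named outcome nowhere.

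**3. Direction.** The expected number in the control arm is zero by construction. Leaving the event out can lower the mH-P count or leave it unchanged, and it cannot change the control count.

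**4. Scale, on assumed leak rates.** The planned arm size is 70 (Sample size section). The article gives no leak rate p, so 1% to 5% is an assumption.

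- Expected leaks = 70 × p.
- Chance of at least one = 1 − (1 − p)^70.

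| Assumed p | Expected leaks | Chance of at least one |
|---|---|---|
| 1% | 0.7 | 50.5% |
| 2% | 1.4 | 75.7% |
| 5% | 3.5 | 97.2% |

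**5. Effect on the share of patients with any complication.** Let b be the share of mH-P patients who have a listed event. If leaks are independent of listed events and are not recorded as one, the omission understates the mH-P share by (1 − b) × p. The article gives no b, so 30% to 50% is assumed.

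- p = 1%: (1 − 0.5) × 1% = 0.5 points to (1 − 0.3) × 1% = 0.7 points.
- p = 5%: (1 − 0.5) × 5% = 2.5 points to (1 − 0.3) × 5% = 3.5 points.

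**6. Would the planned test show it?** Take the largest of these gaps, 30% against 33.5%, with 70 per arm and a two-sided 5% level. The normal approximation gives power Φ[(0.035 − 1.96 × 0.0787)/0.0786] = Φ(−1.52), or about 6.5%. Even if the leaks were counted, the test on the total would almost never single them out.

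**The case against.** The strongest reply is that little is really lost. The Safety section collects adverse events of any kind. Its definition of a serious event covers prolonged hospital stay, danger to life, and important events that may need intervention. The committee's parameters are introduced as all serious adverse events, so the items listed after that phrase need not be exhaustive. A clinically important pyloroplasty leak would therefore be recorded and could reach the committee. This stands. A reader might infer from the six-item list that the whole safety comparison is tilted towards mH-P, and the documents do not support that. They do not rescue the complication outcome either: collecting an event elsewhere does not put it into the defined count, and the article states no between-arm comparison of adverse events.

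A reader might also infer that all three harms named under post-trial care have been left out. That is wrong for two of them. Bile reflux and dumping-type symptoms are planned outcomes in both arms, and the Outcomes section says that patients and symptom assessors are blinded. Classing them as function and symptoms is a legitimate choice. Moving them into a yes/no complication count would count them twice, with no stated threshold for turning 5-point items or a bilirubin level into an event.

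Third, the size is small and rests on assumed rates. This too stands. The chance of at least one leak says whether the gap is likely to matter in practice; it does not measure bias in the comparison. Nor can one say that every such leak would go uncounted, since some patients would have a listed event as well. The low power is not a defence, however. It is the reason why the event needs a line of its own.

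**Conclusion.** The concern holds for one event and one comparison. The definition of postoperative complications does not name leakage at the pyloroplasty site, which the article itself recognises as a harm and which only mH-P patients can have. For that event the key secondary complication comparison can err in one direction only.

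At assumed leak rates of 1% to 5%, this concerns 0.7 to 3.5 expected events in 70 patients. It understates the mH-P complication rate by about 0.5 to 3.5 percentage points if the share with a listed event is 30% to 50%, leaks are independent of listed events, and none is recorded as one. The direction follows from the text; the size does not. The primary endpoint is unaffected, and the wider collection of adverse events, reflux and symptoms remains intact. The change is nonetheless worth making: it is cheap, and the event is the one most specific to the procedure under test.

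**What to change.** - **Outcomes:** add leakage at the pyloroplasty site to the definition of postoperative complications.
- **Oversight and monitoring:** name the same event among the committee's safety parameters, so that the lists there, in the Outcomes section and under post-trial care agree.
- **Reporting:** show pyloroplasty-site leakage within the total and on a separate line, with the control arm marked as not applicable.
- **Bile reflux and dumping-type symptoms:** keep them as the functional and questionnaire outcomes they already are, and present them by arm beside the complications as harms.

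The cost is one protocol line and one case record form field. Since recruitment began in September 2021, the new field would also have to be completed from the records of patients already enrolled. The mH-P complication rate may look slightly less favourable.
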